#### Outcome measures

##### Outcomes of the main study

***Primary outcome: immediate transfer of the practiced skill*** We chose the Melbourne Assessment 2 subscale fluency (MA2_fluency_) as the primary outcome measure for the immediate transfer. The MA2 consists of the four subscales movement range, accuracy, dexterity and fluency [39] and is an adequate measurement for research and clinical use in children with cerebral palsy [40]. The intraclass correlation coefficient of the test-retest reliability of the MA2_fluency_ is 0.96 (95% confidence interval 0.90–0.99), the minimal detectable change is 2 points and the minimal clinically important difference is at least 3 points [40]. Concerning the concurrent validity, Pearson’s correlation coefficients between the MA2_fluency_ and other tests amounted to 0.67 (Bruininks-Oseretsky Test of Motor Proficiency, Second Edition, subtest 3, manual dexterity), 0.76 (Box and Blocks Test) and 0.40 (Paediatric Motor Activity Log–Revised, quality of movement) [40]. The responsiveness of the MA2_fluency_ is high, which is indicated by significant change scores and a high standardised response mean value of 1.84 [40].

From a clinical point of view and in line with literature (e.g. [9]), we consider the transfer to be an important aspect of learning. We hypothesise that MA2_fluency_ will improve when practicing the reaching movements. During the exergames, the participant will be instructed to reach the target by the most direct path, i.e. as fast as possible. This is in line with the MA2_fluency_ scoring criteria, which include jerkiness, tremor and/or reduced speed of movement [41].

Since we considered the MA2_fluency_ to be more sensitive to change instantly after the practice sessions due to the relatively short practice period and to avoid a potential loss to follow-up at later time points, we chose the immediate transfer as the time point of interest for the primary outcome.

One of three trained occupational therapists will score the MA2_fluency_ by analysing the video. The rater will be blinded for the participant’s group allocation, the time point of assessment and the randomisation code. The sum scores will be calculated and used for further analysis.

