##### Feasibility outcomes

In line with recommendations on reporting protocols of pilot and feasibility trials [26], we will apply the following ten specific feasibility criteria:
Are the chosen inclusion criteria specific enough to result in a sample of participants, which is suitable for this pilot study (e.g. are they able to play the exergame)?Is the recruitment rate feasible? Since the main randomised controlled trial would require a large number of participants, it is relevant to know the number of participants that will be recruited during a certain period.The number of children enquired for the study, number of participants recruited, number of complete datasets within 1 year will be recorded and used to calculate recruitment rates.Is the scheduling procedure feasible? The appointments will be planned for 3 weeks for each participant. The person conducting the exergame tests and the MA2_fluency_ always will need to be the same. The same will apply for the person instructing the child during the practice sessions. Absences of personnel (e.g. due to illness, holidays or part-time employment) and the children (e.g. due to illness or short-term planned medical appointments), as well as the availability of the robot and material for the MA2_fluency_ (i.e. whether they are not used for therapy at the time points of the measurements), will need to be considered. Information about whether it is possible to schedule rooms, persons involved and the robot and table for performing assessments will be noted.Is the randomisation procedure feasible? Experiences of the persons involved will be collected and evaluated to answer this question.Is the whole procedure feasible for the participants? The rather time-consuming procedure and the high number of repetitions might be difficult for at least some of the participants because of fatigue or lack of motivation to play the exergames so many times. Both reasons influence motor learning negatively. Therefore, it is important to determine whether the participants included in this study are able to comply the whole study procedure. Information about aborted or shortened sessions or other incidents and their reasons (e.g. pain or discomfort, fatigue) will be taken from the lab journal.Is the handling of the robot feasible? The ChARMin robot has been in use in the clinical and research area since 2015. Since it is a newly developed tool, it is important to evaluate its handling. Any technical issues will be noted and then retrieved from the lab journal.Is the handling of the large amount of data feasible? Information from the assessors and the analyst on the primary outcome will be used.Are the outcome measures responsive and sensitive enough within this setting? Responsiveness analysis of the assessment data will be performed.Is there a confounding influence of parallel therapies within the rehabilitation setting? As the study will be conducted during the inpatient rehabilitation stay, it is important to estimate whether parallel-applied therapies could confound the results. Since an additional control group following usual care would require a larger sample, we chose a design in which each participant acts as its own control and, therefore, we included control measurements during the first week of the study procedure.The changes in the outcomes between week 1 (control week) and week 2 (practice week) will be compared. The kind and number of additional therapies taking place during the different study periods will be recorded to increase the quality of reporting [44].Is it feasible to conduct the main trial with respect to the needed sample size calculated from the data obtained for the primary motor learning outcome? With the data of the primary outcome measure, we will calculate the required sample size for the main trial.

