#### Analysis of feasibility

The ten areas (see outcome measures section) will be evaluated with the information obtained during the study. Only questions 8, 9 and 10 will require statistical analyses to be answered:
8)Responsiveness analysis of the outcome measures for this specific intervention: the data (MA2_fluency_ and exergame test data) of the measurement time point immediately before the first and right after the last practice session will be compared. For internal responsiveness, the standardised response mean will be calculated. For the external responsiveness, a Pearson correlation coefficient will be calculated between the change-scores (i.e. between the two measurement time points) of the MA2_fluency_ and the ChARMin parameter nP_norm_.9)Effect due to the parallel therapies within the rehabilitation setting: We will include data of all participants to test for a significant change in exergame and MA2fluency scores between day 1 and day 3 in week 1 (i.e. without specific intervention, see Fig. 4) using a paired *T* test or Wilcoxon signed-rank test if a non-parametric analysis will be required. Assuming that the participants will have similar therapy schedules during week 1 and 2, and no change is measured during week 1, a change during week 2 could be attributed to the robotic training. However, if outcomes will improve significantly in week 1, changes observed during week 2 will need to be interpreted with caution, as they cannot be attributed to the study’s intervention alone.10)The sample size estimation for the main trial will be calculated according to the formula

$$ n=\frac{{\left({Z}_{\alpha }+{Z}_{\beta}\right)}^2\times 2{\sigma}^2}{{\left({\mu}_1-{\mu}_2\right)}^2}\kern0.75em $$[46].

Where *n*= sample size, *Z*_*α*_= standard normal *z* value for a significance level *α* = 0.05, which is 1.96, *Z*_*β*_ = standard normal *z* value for the power of 80%, which is 0.84. The pooled standard deviation of the pre-and post-intervention differences (both groups) is indicated by *σ*, *μ*_1_ is the mean pre-post-intervention difference of the intervention group 1, *μ*_2_ is the mean pre-post-intervention difference of the intervention group 2.

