#### Analysis of motor learning outcomes of the main trial

As recommended by the CONSORT extension to pilot and feasibility studies, we will report 95% confidence interval estimates of the motor learning outcomes [27], as the study will be most likely underpowered. Hypothesis testing will only be conducted if the recruited sample size is large enough to warrant sufficient statistical power.

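### Item 10 sizes the main trial from the pilot's own observed between-arm difference, so with about 10 children per arm the answer to feasibility question 10 is mostly sampling error

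*Protocol article*

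**What the plan says.** Analysis of feasibility, item 10, gives n = (Zα + Zβ)² × 2σ² / (μ1 − μ2)². The significance level is "0.05, which is 1.96", and Zβ is the "value for the power of 80%, which is 0.84". The other inputs are defined as follows:

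- σ: "The pooled standard deviation of the pre-and post-intervention differences (both groups").
- μ1: it "is the mean pre-post-intervention difference of the intervention group 1".
- μ2: it "is the mean pre-post-intervention difference of the intervention group 2".

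Feasibility outcomes, question 10, names the source of these values: "With the data of the primary outcome measure, we will calculate the required sample size for the main trial". The abstract and the question list in the Background say the same. Target sample size anticipates 20 participants, 10 per group.

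Two other sections bear on the point. Outcomes of the main study reports for the fluency subscale that "the minimal detectable change is 2 points and the minimal clinically important difference is at least 3 points". Analysis of motor learning outcomes of the main trial plans 95% confidence intervals for the motor learning outcomes, "as the study will be most likely underpowered".

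**The concern.** Both the effect and the SD in the formula are pilot estimates from about 20 children. The SD is a usual thing to learn from a pilot. The effect is not, because a pilot of this size hardly constrains it. The protocol accepts this for the outcome analysis, where it prefers intervals to tests. Item 10 nevertheless takes the same between-arm difference as a single value, squares it and divides by it. A small error in the difference then becomes a large error in n, and the squaring removes the sign.

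The required size is a declared product of the pilot. If it is largely chance, question 10 gets an answer that looks quantitative but says little about whether the main trial is feasible. The main trial could be planned far too small, or could look out of reach, because of sampling error alone.

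**Working it through.** **Inputs from the protocol.** Two-sided α = 0.05 (z = 1.96), power 80% (z = 0.84), 10 per arm. The protocol gives no main-trial n to reproduce, no planned effect and no SD of change.

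**The formula itself.** (1.96 + 0.84)² × 2 = 15.68, so n = 15.68 / d² with d = (μ1 − μ2)/σ. This is the standard per-group formula. It gives 175 per group at d = 0.3, 63 at d = 0.5 and 25 at d = 0.8. The constants and the algebra are correct; the difficulty is where d comes from.

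**Precision of the observed difference.** With 10 per arm and 18 degrees of freedom, the 95% half-width in SD units is t(0.975; 18) × √(2/10) = 2.101 × 0.447 = 0.94. For example, an observed difference of 0.5 SD has an interval of −0.44 to 1.44. The upper end gives 15.68 / 1.44² = 7.6, or 8 per group. The interval also contains zero, where no finite n exists.

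**What the rule returns.** Simulated pilots with normally distributed changes: observed difference ~ N(d, 2/10) in SD units, pooled variance ~ χ²(18)/18, both put into the item 10 formula. The true d is an assumption.

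| Assumed true d | n needed per group | Median n returned | 5th–95th percentile | n gives under 50% true power | Observed sign opposite to true |
|---|---|---|---|---|---|
| 0.3 | 175 | 108 | 13 to about 12,000 | 45% | 25% |
| 0.5 | 63 | about 58 | 9 to about 5,500 | 33% | 13% |
| 0.8 | 25 | 24 | 6 to about 850 | 25% | 4% |

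The upper percentiles move by a few per cent between simulation runs. Two columns can be checked by hand. The probability of a reversed sign is Φ(−d/√0.2), which at d = 0.5 is Φ(−1.118) = 0.13. Power of 50% at d = 0.5 needs 2 × (1.96/0.5)² = 30.7 per group, so an n of 30 or fewer falls short. At d = 0.5 only 12% of pilots return an n within 25% of the 63 needed. With no true effect at all, the rule still returns a finite n, with a median of 167 per group.

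**With the target fixed and only σ taken from the pilot.** Suppose the true SD of change equals the target, for example 3 points each (the SD is assumed). Then 15.68 per group is needed, rounded up to 16. Sampling error in σ alone gives a 95% range for n of 8 to 28. For the same standardised effect, d = 1, the remaining noise is about 3.5-fold. Under the current rule at d = 0.5 the 95% range runs from 7 to about 22,000.

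**Small-n caution.** For 3 points with SD 2, the formula gives 15.68 × 4/9 = 6.97, or 7 per group. A t-based calculation gives a power of about 73% at 7 and needs 9 per group to reach 80%.

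**The case against.** **There is no automatic rule.** A reader might infer that a chance-large difference would launch an underpowered trial and a chance-small one would stop the programme. The protocol does not say so. Question 10 is one of ten feasibility questions, and the Conclusion leaves whether and how to run the main trial to a later decision. The calculation can also be redone from the same data. This stands, and it lowers the severity.

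**The confidence intervals are reported.** A reader might infer that a reversed difference would go unnoticed. That is too strong: the primary outcome is one of the motor learning outcomes for which intervals are planned, so its direction and imprecision should be visible. What remains is that nothing carries this uncertainty into n.

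**No direction is named.** Potential risks and benefits for the participants says it is not known which practice order is better, and z = 1.96 is two-sided. It is therefore not accurate to speak of the wrong arm. The supportable statement is that the observed sign can be opposite to the true one and that n does not show it.

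**The effects are assumed, and 10 per arm is only anticipated.** Both are true. At 0.8 SD sign reversal is minor, at 4%, but n still runs from 6 to about 850, so a large effect does not rescue the method.

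**The quoted benchmarks may not suit.** It is tempting to read the 2- and 3-point figures as ready-made targets. The protocol reports them as properties of the scale. Detectable change reflects measurement error, and both arms do the same number of trials and differ only in order, so a 3-point difference between arms needs its own argument. This also stands and shapes the fix.

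**Conclusion.** The concern holds: item 10 fixes a method that cannot give a dependable answer to question 10 at the pilot's anticipated size. The half-width of ±0.94 SD follows from 10 per arm alone. The simulated figures rest on normally distributed changes and on assumed true effects of 0.3 to 0.8 SD, because the protocol states none. Across that range, 25% to 45% of pilots would yield an n with under 50% true power.

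The point is not one left to an unseen analysis plan, since the article states the formula and the source of its inputs. It should be fixed, but it does not threaten the pilot: no participant, no pilot outcome and none of the other nine feasibility questions depends on it. The documents do not support saying that the pilot would mechanically start or stop the main trial, or that a 2- or 3-point difference is already the right target.

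**What to change.** Amend item 10 in four respects.

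1. **Target.** State in advance a between-arm difference worth detecting, with its justification, and do not use the observed μ1 − μ2 for sizing. The 3-point important difference can inform it if its use for a between-arm contrast is argued. The 2-point detectable change should not be the target by itself.
2. **Scale.** Put the target and σ on the scale that is tested. The Primary outcome analysis compares the relative change, (MA2_4 − MA2_3)/MA2_3, whereas item 10 speaks of pre-post differences. Either express the target as relative change, or use raw fluency points and align the primary analysis with them.
3. **SD.** Take only σ from the pilot. Report n at the estimate and at an upper confidence limit, with a t-based calculation where n is small. For illustration, with a 3-point target and an assumed SD of 3, the one-sided 80% upper limit on 18 degrees of freedom is 3 × 1.18 = 3.55, and n by the formula rises from 16 to 15.68 × 3.55²/9 = 22 per group.
4. **Description.** Report the observed between-arm difference with its 95% confidence interval as description only.

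The cost is a few sentences in item 10 and, if raw points are chosen, a matching edit to the primary analysis. No new data are needed. The sponsor must defend a target beforehand, and the resulting n may be less favourable.

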#### Analysis of motor learning outcomes of the main trial

As recommended by the CONSORT extension to pilot and feasibility studies, we will report 95% confidence interval estimates of the motor learning outcomes [27], as the study will be most likely underpowered. Hypothesis testing will only be conducted if the recruited sample size is large enough to warrant sufficient statistical power.

##### Primary outcome

***Immediate transfer*** The relative difference $$ \left(\frac{MA{2}_4- MA{2}_3}{MA{2}_3}\right) $$ of the MA2_fluency_ sum score between the time point right before the first practice session (MA2_3_) and the time point immediately after the last practice session (MA2_4_) will be compared between the groups. A *T* test (or Mann-Whitney *U* test, if data are not normally distributed) will be performed.

##### Secondary outcomes

For all secondary outcomes, a multifactorial repeated measures analysis of variance (ANOVA) with ‘practice group’ and ‘time point’ as factors will be conducted over all the time points. A post-hoc analysis (Bonferroni correction for multiple comparisons) will be used to test for significant changes between the appropriate time points.

***Delayed transfers*** The MA2_fluency_ sum scores will be compared between the time point right before the first practice session, 1 day after the last session (1-day-delayed transfer), and 1 week after the last session (1-week-delayed transfer).

***Immediate retention, delayed retentions, acquisition*** For the several retention time points and the acquisition, the parameter nP_norm_ (obtained during the exergame tests and the practice sessions, respectively) will be evaluated. Comparisons will be made between the data obtained during the exergame tests right before the first practice session with the data from immediately after the last practice session (immediate retention), 1 day after the last practice session (1-day retention), and 1 week after the last practice session (1-week retention). For the acquisition, all the data points obtained during the practice trials will be compared.

##### Assumptions

Generally, statistical testing is only performed in case of sufficient statistical power. For a *T* test, the normal distribution of the data will be required, which will be tested with a Shapiro-Wilk test. For an ANOVA, the homoscedasticity of values of the groups and normal distribution of the population of the residues will be tested with the Levene test and the Shapiro-Wilk test, respectively.

## Discussion

We aimed to present the study protocol of a randomised controlled single-blinded pilot trial to explore the feasibility of testing the contextual interference effect while practicing robot-assisted upper limb tasks with exergames in a representative sample of children with congenital or acquired brain lesions.

### Putting the pilot study in the wider context

It is common that different motor tasks are practiced within the same therapy session in paediatric neurorehabilitation. Human movement is variable (e.g. [19]) and variability generally seems to be beneficial for learning of new motor skills [47]. Despite this, high-level evidence about the contextual interference effect in children in general and particularly in children with brain lesions is missing [20]. If children with congenital or acquired brain lesions would respond similarly as healthy adults to the contextual interference effect, random practice would be more beneficial compared to blocked practice at retention and transfer. On the long-term, this knowledge could contribute to the optimisation of treatment protocols leading to improved clinical outcomes in children undergoing neurorehabilitation.

All rehabilitation goals are individual, yet participation [48] and independence in daily life are often mentioned as the most important aims for the rehabilitation of children [49]. The importance of generalisability of motor improvements (i.e. the result of motor learning) and the retention thereof in the daily life of the child is probably not a matter of dispute. Yet, there is a gap between the somewhat constrained reaching movement during an exergame with a robot that is limited to specific movement directions and a goal-directed reaching movement in daily life. Or, in the language of the International Classification of Functioning, Disability and Health [50], practicing ‘body functions’ or ‘capacity’ in a robot might not directly influence ‘performance’ in a daily life environment. While in the robotic condition, the starting position is relatively fixed and the number of movement directions is prescribed and somewhat constrained, reaching in daily life has not such limitations, which leads to many more movement opportunities [51], including numerous movement directions requiring movement control over multiple joints. Furthermore, the use of upper extremities in daily life is mostly a bimanual matter in persons without neurological deficits [52, 53]. While there will much more questions coming up along the way, a randomised controlled trial, as we described it in this protocol, might answer the first question. As there is not enough knowledge available to start with such a study, the conduct of a pilot study is inevitable. Concludingly, this protocol of the planned pilot study is the first step of a series of successive questions and, hopefully, answers, which ultimately leads to an optimised transfer of motor learning improvement into everyday life performance.

### Potential risks and benefits for the participants

It has been stated that scientists need to develop sensitivity for the risks and benefits of the participants when volunteering for a trial [54]. Currently, we do not know whether the blocked or random practice order would be more beneficial. Nevertheless, we assume that the practice schedule described in this study protocol could lead to an improvement in motor functions. Despite that participants will practice only three sessions, according to literature, the resulting 1440 repetitions should induce motor learning as 500 repetitions led to motor learning effects in adults after stroke [37]. Therefore, for all the children participating in this study, a direct benefit can be expected. Especially for such a vulnerable population as children with neurological impairments, the risks of participating in a study should be minimal or, if greater, should be outweighed by the anticipated benefit [55]. Our study provides a safe setting, and we expect no severe adverse events. Potential risks might be fatigue, muscle soreness, a more challenging rehabilitation schedule due to a higher number of sessions than usual and skin irritations due to pressure and friction of the cuffs. The risk-benefit trade-off of this pilot study seems balanced and therewith justifiable.

